### Randomisation

In four of the Medicare Locals/Divisions of General Practice, enrolled general practices are randomly allocated to the control group or Intervention 1 at a ratio of 1:2. In the other three Medicare Locals/Divisions of General Practice, practices are randomly assigned to the control group or Intervention 2 at a ratio of 1:2. A single type of intervention is tested in each Medicare Local/Division of General Practice as a result of two practical constraints: (1) care facilitators included in Intervention 2 are required to work with four or five practices within a single geographic area in order to work effectively; and (2) Medicare Locals/Divisions of General Practice would find it difficult to enrol and support practices using two different interventions, given that Intervention 1 and Intervention 2 comprise multiple components. Randomisation is applied after recruiting each group of three practices in a combined Medicare Local/Division of General Practice and Region stratum, where Region refers to urban or rural area. This helps to mitigate the potential bias created by testing only one intervention in each Medicare Local/Division of General Practice. Randomisation is applied separately for urban and rural practices within each Medicare Local/Division of General Practice because it is expected that service use and availability will differ by region. To approximate equality of sample sizes in each group, block randomisation is used with computer-generated, randomly permuted blocks of three. A researcher who is not involved in the implementation of the project and is blinded to the identity of the practices performs this task.

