Practices assigned to Intervention 2 experience four changes: access to cdmNet; altered funding arrangements; the provision of a care facilitator; and access to training and capability building. Coordinated care is facilitated through the use of the cdmNet decision support service (as in Intervention 1), but with the addition of risk stratification. Patients are stratified into one of four risk categories based on whether they have complications associated with diabetes (e.g., peripheral neuropathy, background diabetic retinopathy, foot ulceration) and whether their diabetes is under control (uncontrolled diabetes requiring additional allied health services is defined as either HbA1c >7.5% [>58.5 mmol/mol], systolic blood pressure >150 mmHg, total serum cholesterol >5.0 mmol/l, or systolic blood pressure >140 mmHg plus total serum cholesterol >4.5 mmol/l). The four risk categories are characterised as follows: (1) not complex and within range; (2) complex and within range; (3) not complex and out of range; and (4) complex and out of range (see Figure 2). The care plan that is generated for the patient reflects the minimum care needs of individuals in their respective strata, as informed by best practice guidelines. Care in Intervention 2 is also coordinated through the provision of a full-time care facilitator (a tertiary-qualified health professional with experience in primary health care delivery), whose role is to assist the multidisciplinary team in delivering care in accordance with the agreed care plan. The care facilitator has a case load of approximately 300 to 400 patients across all four risk strata.

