### Sample size calculation

A minimum sample size of 150 practices (or 50 practices per trial arm) and 3,750 patients (or 1,250 patients per trial arm) would allow a difference of 0.25 percentage points of HbA1c to be detected between any two trial arms with 80 percent power. The sample size is based a standard deviation of HbA1c of 1.4 percent, 20 percent attrition over 18 months, a design effect of 3.45 based on an ICC of 0.05 (correlation between baseline and 18-month HbA1c), and a two-sided alpha level set at 0.025 to adjust for pairwise comparisons.

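### The sample-size statement does not follow from its own inputs: as printed, 1,250 patients per arm gives about 46% power for 0.25 points, not 80%, and neither the design effect nor the ICC is properly explained

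*Protocol article*

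**What the plan says.** The Sample size calculation section of the protocol article sets the size as "A minimum sample size of 150 practices (or 50 practices per trial arm) and 3,750 patients (or 1,250 patients per trial arm") and says that this "would allow a difference of 0.25 percentage points of HbA1c to be detected between any two trial arms with 80 percent power". For the outcome it assumes "a standard deviation of HbA1c of 1.4 percent", and it expects one patient in five to be lost by 18 months. For clustering it uses "a design effect of 3.45 based on an ICC of 0.05 (correlation between baseline and 18-month HbA1c"). The significance level is given as "a two-sided alpha level set at 0.025 to adjust for pairwise comparisons". The Recruitment section also expects fifty practices in each group.

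The Primary outcome section defines the endpoint as the between-group difference in HbA1c change and repeats that the study has power for 0.25 points between any two groups. The Main analysis section plans a linear mixed model, with the time-by-group interaction as the test of effect. The article gives no figure for variation in practice size, and no correlation other than the 0.05.

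**The concern.** Three things in one short paragraph do not fit together.

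- **Size and power.** The printed inputs call for about twice the printed sample.
- **Design effect.** 3.45 does not correspond to the planned number of patients per practice, unless practice sizes vary by an amount that is not stated.
- **ICC.** The parenthesis describes a within-patient correlation over time. A design effect for clustering needs the correlation between patients of the same practice.

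This is the article's only justification of size for the primary endpoint. A reader told that power is 80% expects a true 0.25-point difference to be missed one time in five. If power is lower, a null result would be taken as stronger evidence of no effect than it is.

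**Working it through.** **Inputs** (all from Sample size calculation): difference 0.25; SD 1.4; two-sided alpha 0.025 (z = 2.2414); power 80% (z = 0.8416); attrition 20%; design effect (DE) 3.45; ICC 0.05; 50 practices and 1,250 patients per arm.

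**1. Attempt to reproduce 1,250.**

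Uninflated n per arm = 2 × (2.2414 + 0.8416)² × 1.4² / 0.25² = 596.

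With clustering: 596 × 3.45 = about 2,057. With attrition: 2,057 / 0.8 = about 2,571 per arm. The article states 1,250, so the printed inputs ask for about 2.06 times as many.

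**2. Power at the stated size.**

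Completers per arm = 1,250 × 0.8 = 1,000. Power = Φ(0.25 / (1.4 × √(2 × DE / 1,000)) − 2.2414).

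At DE 3.45 the standard error is 0.1163, so power = Φ(2.150 − 2.241) = 46%. The difference detectable with 80% power is 3.083 × 0.1163 = 0.36.

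**3. What 3.45 implies.**

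For equal practices, DE = 1 + (m − 1) × ICC, so m = 1 + (3.45 − 1) / 0.05 = 50. The plan gives 1,250 / 50 = 25 enrolled per practice, or 20 after attrition. Hence DE = 1 + 24 × 0.05 = 2.20, or 1 + 19 × 0.05 = 1.95.

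| Design effect | Basis | Power for 0.25 | Detectable at 80% | Needed per arm |
|---|---|---|---|---|
| 3.45 | as printed | 46% | 0.36 | 2,571 |
| 2.20 | 25 per practice, equal | 67% | 0.29 | 1,639 |
| 1.95 | 20 per practice, equal | 73% | 0.27 | 1,453 |

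A t-test on 98 cluster degrees of freedom lowers these powers slightly, to 45%, 66% and 72%.

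**4. Unequal practice sizes.**

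With coefficient of variation CV, DE = 1 + ((1 + CV²) × m − 1) × ICC. For m = 25 and CV = 1 this is 1 + 49 × 0.05 = 3.45. So 3.45 can be matched to a mean of 25, but only with an unstated CV of about 1, and power then stays at 46%.

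**5. Other variants.**

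- DE 3.45 ignoring attrition: 56% power.
- DE 3.45 with two-sided alpha 0.05: 58%.
- DE 1.95 with two-sided alpha 0.05: 82%, but this contradicts both the printed design effect and the printed alpha.

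**6. Gain from baseline HbA1c** (assumed, not stated in the article; the same variance factor is applied throughout).

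80% power at 1,000 completers needs a variance factor of 1,000 / (596 × DE): 0.486 at 3.45, 0.76 at 2.20 and 0.86 at 1.95.

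- Baseline-adjusted analysis, factor 1 − ρ²: ρ of about 0.72 at DE 3.45, or 0.37 to 0.49 at DE 1.95 to 2.20.
- Change score, factor 2(1 − ρ): ρ of about 0.76 at DE 3.45, or 0.57 to 0.62 at DE 1.95 to 2.20.

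The only correlation printed is 0.05. Used as a baseline correlation at DE 3.45, it gives 46% (adjusted) or 25% (change score).

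**The case against.** The strongest defence is that the parenthesis is what remains of a dropped input. The endpoint is change, the test is a time-by-group interaction, and the text names a baseline-to-18-month correlation. A moderate value would be enough at design effects of 1.95 to 2.20. This is a plausible explanation, but not a defence of the text: the value is not given, the label is attached to the ICC, and the reader cannot check the result. The paragraph needs rewriting either way.

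It is also fair to say that 3.45 is unexplained rather than proven wrong, because variation in practice size could produce it. A reader might infer that the number of practices per arm, also 50, was used as the cluster size, or that a factor of two was lost: 50 practices of 50 patients, or 2,500 per arm, would give about 79% power at 3.45. Both are possible; the article establishes neither.

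A reader might also see a contradiction with the facilitator figures: "The care facilitator has a case load of approximately 300 to 400 patients across all four risk strata", while "care facilitators included in Intervention 2 are required to work with four or five practices within a single geographic area", which implies 300 / 5 = 60 to 400 / 4 = 100 patients per practice. The article does not support this reading. The caseload concerns a staff role in Intervention 2 only, and the 25 per practice follows from a stated minimum. Nor would such sizes reduce power if they held in all arms, since the sample grows as well. Sixty per practice gives 50 × 60 × 0.8 / 3.95 = 608 effective patients per arm and about 81% power. One hundred per practice, 80 retained, gives 4,000 / 4.95 = 808 and about 91%.

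**Conclusion.** The point holds. The stated 80% power does not follow from the stated inputs: they need about 2,571 patients per arm, or give 46% power at 1,250. With the design effect taken from the plan's own cluster size and equal practices, power is 67% to 73%, still below 80%. A true 0.25-point difference would then be missed 27% to 54% of the time, against the 20% that the article implies. Separately, the ICC is misdescribed.

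These figures assume 50 against 50 practices, a normal approximation and no gain from baseline HbA1c. Two stronger conclusions are tempting but unsupported. The 46% is the consequence of the printed inputs, not the trial's true power. Equally, 1.95 and 73% are not the single correct values: they assume equal practices and a comparison of follow-up means only. Variation in practice size would lower the power, and a sufficient baseline correlation would raise it.

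**What to change.** Rewrite the Sample size calculation paragraph and bring the power claim under Primary outcome into line with it:

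1. Define 0.05 as the within-practice ICC of HbA1c.
2. State the mean number of patients per practice, enrolled and analysed, and any assumed variation in it, and derive the design effect from these.
3. If a baseline-to-18-month correlation was used, give its value as a separate input, with the variance formula that matches the planned time-by-group analysis.
4. Restate the power for 0.25 points, or the detectable difference, that 50 practices of 25 patients per arm delivers. With no gain from baseline correlation this is 46% to 73%, or 0.36 to 0.27 points, depending on the design effect.

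The cost is one reworded paragraph and one aligned sentence. Enrolment, endpoint and analysis do not change. The stated power becomes less favourable unless a documented baseline correlation supports it.

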### Statistical analysis

#### Main analysis

Descriptions of participants’ baseline characteristics (e.g., demographic data, comorbidities and clinical metrics) will be reported by treatment group. Categorical variables will be summarised by frequencies and percentages. Continuous variables will be summarised by means and SEMs, or non-parametric equivalents. All primary statistical analyses will be performed on an intention-to-treat basis. The continuous variable—HbA1c at approximately 18 to 22 months—will be compared between groups using a linear mixed effect model with adjustment for clustering and stratification status (Medicare Local/Division of General Practice and metro/rural practice location). The time/group interaction parameter will be used to formally test for an intervention effect. Secondary outcomes (excluding economic sustainability and value for money) will be analysed similarly. These findings will be presented in accordance with the reporting requirements outlined in the Consolidated Standards of Reporting Trials (CONSORT) statement - extension for cluster randomised trials [21].

#### Economic evaluation

Economic sustainability will be assessed by estimating the total mean per patient cost (including co-payment) and cost to government (separately for the Commonwealth and State governments) of patients in each of the three treatment groups. This will allow the DCP to estimate cost and budget impacts of the intervention models. Data will be sourced from Medicare Australia, State governments (for hospital in-patient, emergency and outpatient services), the patient diary and the NDSS. Depending on how well participants are matched across groups at baseline, some statistical adjustment may be necessary. Each person will be allocated to a diabetes disease stage (based on risk and morbidity profile), and the mean annual cost at each disease stage will be estimated across all three groups. The rate of progression in disease stage over the course of the study will be described for each patient and compared across groups to test for any between-group differences. If differences are detected, this will be used to model the downstream cost and budget implications of the three models of care.

A cost utility analysis will be conducted using the AQoL-4D to derive quality of life utility scores and to measure any change across the trial. Results for the three groups will be compared to identify any differential change in quality of life that can be multiplied by time to generate quality-adjusted life year (QALY) gain or loss for each intervention group. A quality of life utility score will be calculated for each disease stage (from persons in the disease stage), with a lower quality of life expected with more advanced disease. If a difference in the rate of disease progression is identified, this will be used to model the downstream impact on QALYs. The cost of implementing the model will be derived from trial administrative data and health care costs as described above. These costs will be combined with QALYs (within the trial and modelled beyond the trial) to estimate cost per QALY gain if it is found that the intervention is more expensive but delivers greater quality of life.

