**Figure 2 F2:**
[figure not shown]
**Overview of risk stratification categories**^**#**^**.** HbA1c = Glycosylated haemoglobin; SBP = Systolic blood pressure. ^#^These risk stratification categories apply to participants with type 2 diabetes. Participants diagnosed with type 1 diabetes will be provided with the same level of resources as persons in the ‘out-of-range/complex’ category. Newly diagnosed patients will receive the support designated from their category plus additional support for introductory needs.

The altered funding arrangements that are tested in Intervention 2 comprise three components: flexible funding for general practices; pay-for-performance payments for general practices; and flexible funding for allied health professionals. Flexible funding for general practices provides upfront, lump sum funding for all patients who are voluntarily enrolled in the trial at a given practice, which is adjusted according to the risk of the patient population. This funding is used to fund care planning activities for those patients who require it (and is paid once a patient is enrolled rather than for completion of any specific activities) but it does not replace usual GP consultation fees covered by Medicare (Australia’s universal healthcare system). Pay-for-performance payments reward practices for improvements in patient clinical outcomes, meeting pre-defined levels of positive patient experience and completing pre-defined clinical processes. Flexible funding for allied health professionals is accessed on a fee-for-service basis, drawing on a risk-adjusted allowance for each patient. Participants in the control group, Intervention 1 and Intervention 2 will receive their respective care for a period of approximately 18 to 22 months (depending on when they are risk stratified).

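### The downstream cost and budget model runs only if a difference in progression is detected, and pooled stage costs would need each arm's programme cost added

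*Protocol article*

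**What the plan says.** All of the following is in the protocol article, Economic evaluation, unless another section is named.

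- Average cost per patient and cost to government are estimated "of patients in each of the three treatment groups". The text says that this gives the cost and budget impacts of the models. No condition is attached.
- Patients are staged individually: "Each person will be allocated to a diabetes disease stage (based on risk and morbidity profile"). For the price of a stage, the section goes on to say that "the mean annual cost at each disease stage will be estimated across all three groups".
- Progression through the stages is compared across groups. Then: "If differences are detected, this will be used to model the downstream cost and budget implications of the three models of care".
- In the cost-utility paragraph, "A quality of life utility score will be calculated for each disease stage (from persons in the disease stage"). Downstream QALYs are modelled under the same condition of an identified difference in progression.
- Also in that paragraph: "The cost of implementing the model will be derived from trial administrative data and health care costs as described above". These costs are combined with QALYs both within the trial and modelled beyond it. The paragraph on downstream cost and budget does not mention implementation cost.
- In the Interventions section, Intervention 2 adds a full-time care facilitator and pay-for-performance payments. It also adds upfront practice funding "which is adjusted according to the risk of the patient population", and allied health funding "drawing on a risk-adjusted allowance for each patient".

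**The concern.** Two features of the downstream model matter.

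First, a detection rule decides whether the model exists at all. Failure to detect a difference in progression is not evidence that there is none. A budget projection also does not need such a difference to be informative: the facilitator goes on costing money each year even if progression is identical.

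Second, if the model runs with one price per stage shared by all arms, the arms can differ only in stage mix. Intervention 2 is designed to cost more for a patient at a given stage. A shared price spreads that extra cost over all three arms, and it then largely cancels in the comparison. Slower progression would be credited to Intervention 2 in full, while its running cost would hardly be charged.

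The Research objectives ask whether the interventions are economically sustainable and scalable, and the Discussion asks whether national roll-out of Intervention 2 is worthwhile. The downstream model is the part of the budget work that looks past 18 to 22 months.

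**Working it through.** The plan gives no figure for this point, so there is none to reproduce. The checks below show the size of each effect under stated assumptions.

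**The detection condition**

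Inputs from the Sample size calculation: 1,250 patients per arm, 20% attrition, design effect 3.45 (set for HbA1c and borrowed here), and 3,750/150 = 25 patients per practice. Assumed: 5-20% of control patients progress, a true relative reduction of 25%, and two-sided 0.05, because the plan gives no threshold for detection. As a milder alternative I assume an ICC of 0.01, so the design effect is 1 + 24 × 0.01 = 1.24.

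- Completers per arm: 1,250 × 0.8 = 1,000.
- Effective n per arm: 1,000/3.45 = 290, or 1,000/1.24 = 806.
- z = (p0 − p1)/√{[p0(1 − p0) + p1(1 − p1)]/n}, and power = Φ(z − 1.96).
- Example, 5% against 3.75%, n = 290: 0.0125/√(0.0836/290) = 0.0125/0.0170 = 0.74, so power is 0.11.
- Example, 20% against 15%, n = 290: 0.05/√(0.2875/290) = 0.05/0.0315 = 1.59, so power is 0.36.

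| Control progression | Design effect 3.45 | Design effect 1.24 |
|---|---|---|
| 5% | 0.11 | 0.23 |
| 10% | 0.19 | 0.43 |
| 20% | 0.36 | 0.75 |

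At two-sided 0.025 the ranges are 0.07-0.26 and 0.16-0.66.

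**Pooled stage prices**

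Let b be the ordinary cost at stage s, a the extra cost of Intervention 2 per patient-year, and w the share of stage-s patients who are in Intervention 2. The pooled price is b + a·w. The part of a that reaches the modelled difference, Intervention 2 minus control, is Σ(p2 − p0)·a·w over stages. The true value for a flat add-on is a.

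Assumed: equal arms, four stages with 25% of patients in each, a = 100 as a scale only, and a shift from the worst to the best stage in Intervention 2 alone.

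- No shift: 0 of 100. Each arm's price carries 33.3, which cancels.
- 5 points: 5 × (0.30/0.80 − 0.20/0.70) = 0.45 of 100.
- 10 points: 10 × (0.35/0.85 − 0.15/0.65) = 10 × (0.412 − 0.231) = 1.8 of 100.
- 20 points: 20 × (0.45/0.95 − 0.05/0.55) = 20 × (0.474 − 0.091) = 7.7 of 100.

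With a different starting mix, .30/.25/.25/.20 moving to .40/.25/.20/.15, the result is 10 × 0.40/1.00 − 5 × 0.20/0.70 − 5 × 0.15/0.55 = 4.00 − 1.43 − 1.36 = 1.21 of 100.

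The share passed on depends neither on the size of a flat add-on nor on the ordinary stage costs. If stage costs are estimated by arm, or programme cost is added by arm, all 100 of 100 is passed on.

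**Which reading of the stage costs**

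Where the section means by arm it says so ("of patients in each of the three treatment groups"), and the matching utility is defined by stage with no mention of arm ("A quality of life utility score will be calculated for each disease stage (from persons in the disease stage"). Both favour pooling. The words could still mean within each of the three groups.

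**The case against.** The strongest reply has four parts.

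1. *The budget paragraph never says that stage costs are the only price in the model.* The data sources listed before the stage costs are Medicare, the States, the patient diary and the NDSS. Implementation cost is derived separately from administrative records. The authors may intend to pool ordinary health care cost and add programme cost by arm, and then nothing cancels. This stands as a possible reading. But the text does not say that programme cost enters the downstream budget. Inside a pooled price it largely cancels, and outside that price it is absent unless added.

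2. *The extra cost is counted elsewhere.* This stands. Costs and budget impacts by arm are planned unconditionally, and implementation cost enters the cost-utility analysis. A reader might infer that the economic evaluation as a whole loses nearly all of Intervention 2's extra cost, or that the plan contains an arithmetic error. The document supports neither. However, the estimate by arm is not described as a projection beyond the trial, and downstream QALYs carry the same condition.

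3. *The condition is a modelling choice: with no established difference there is nothing to project.* This holds for the saving from slower progression. It does not hold for the yearly cost of running the model of care, and it discards the uncertainty in the progression estimate.

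4. *An article condenses.* Silence on programme cost could be put down to that. The detection condition cannot, because it is a stated rule.

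**Conclusion.** The point holds as a cheap improvement. The firm part is the detection condition, which applies whichever way the stage costs are read: without a detected difference in progression, this model gives no downstream cost or budget. Under the assumptions above, a true 25% reduction would be missed more often than found at the stated design effect (detection 11-36%). Under the milder assumed design effect, detection ranges from 23% to 75%. These figures rest on assumed progression rates and on a design effect borrowed from HbA1c.

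The second part is conditional. If stage costs are pooled and no programme cost is added by arm, then between none and about 8 of every 100 of a flat add-on reaches the modelled difference for shifts in stage mix of up to 20 points. No single percentage should be quoted, because the result depends on an unknown stage mix and on a reading that the text leaves open. How much of Intervention 2's funding recurs each year is also not stated: practice funding is paid at enrolment, while the facilitator is a continuing post.

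**What to change.** In the Economic evaluation section, make two changes.

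- Replace the conditional sentences on downstream cost, budget and QALYs with a statement such as: downstream cost, budget and QALYs will be modelled for all three groups from the estimated progression in each group, carrying its uncertainty interval, whether or not a difference is detected.
- State the pricing. Preferably, estimate stage costs separately by group, with programme cost from trial administrative data included. If pooling is wanted for precision, pool usual health care costs only and add each group's yearly programme cost, keeping that cost out of the pooled part so that it is not counted twice. Pooling usual costs still averages away any saving within a stage, which is the reason to prefer costs by group.

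The change needs no new data and little extra analysis. Stage costs by group rest on about a third of the patients, so with equal arms their standard errors are about √3 = 1.73 times larger. The projections will have wider intervals, but they will always be reported.
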